## Abstract

**Background:**

Cognitive impairment and depression frequently occur after spinal cord injury (SCI) and adversely affect functional independence and quality of life. There is a lack of research in addressing this important area in SCI rehabilitation/care. The home-based Action Observation and Motor Imagery (AOMI), a form of neurorehabilitation, was developed grounded in theoretical foundations and practical evidence, rendering it especially suitable for adults with SCI. This study aims to evaluate the feasibility, acceptability, and preliminary effects of this innovative intervention on SCI adults’ cognitive function and depression, while also exploring the underlying neural mechanisms through multimodal magnetic resonance imaging (MRI).

**Methods:**

This is an assessor-blinded, two-arm pilot randomized controlled trial with repeated measures (pre-, post-intervention, and 1-month follow-up). In total, 46 participants will be randomly assigned to either the intervention group, which will receive an 8-week AOMI intervention combined with basic wheelchair exercises, or the control group, which will watch landscape videos and perform basic wheelchair exercises. The feasibility of study procedures will be assessed by examining the recruitment, dropout, and retention rates. The acceptability of interventions will be evaluated by the adverse events record, satisfaction, and adherence rate. The primary outcomes of intervention effectiveness include global cognitive function and depression; secondary outcomes include neurocognitive domains, multimodal MRI findings, chronic pain, self-efficacy for exercise, and motor imagery ability.

**Conclusion:**

The study findings will preliminarily determine the effects of AOMI in SCI rehabilitation. Multimodal MRI data will elucidate the neuroplastic changes and functional reorganization occurring in the brains of the SCI population following the intervention.

**Clinical trial registration:**

ClinicalTrials.gov, identifier NCT06708026.

## Introduction

1

Spinal cord injury (SCI) is a kind of neurological disorder that leads to partial or complete loss of sensory and/or motor functions below the injured level (1). Over 20 million individuals worldwide are living with SCI, and this number continues to increase each year (1). Advances in healthcare services have extended life expectancy for SCI survivors, with nearly 50% surviving 40 years post-injury (2). With the rise in life expectancy, survivors have an increased demand for rehabilitation, community reintegration, and returning to school and work. Cognitive function plays an important role in the successful rehabilitation procedure, as it involves intensive learning and the employment of new skills. However, approximately 30%–60% of adults with SCI suffer from cognitive impairment, with 16% exhibiting severe cognitive impairment (3). Cognitive impairment can develop in individuals with SCI of any age and may occur during both acute and chronic phases (4).

Research has shown that SCI survivors who have cognitive impairment are more likely to experience depression after transitioning back into the community compared to those with normal cognitive function, highlighting the strong link between cognitive function and depression in this population (4). Cognitive impairment, especially in attention, could serve as a gateway for negative thoughts and biases, constituting an internal stressor that maintains the depressive state (5). Depression could also affect cognitive function, including information processing and reasoning (5). There are some joint neural mechanisms behind cognitive impairment and depression following SCI. Longitudinal functional magnetic resonance imaging (fMRI) studies have revealed that SCI can lead to a progressive reduction of brain regions, including the cerebellar cortex, medial prefrontal cortex, and anterior cingulate cortex. These areas are essential for emotional processing and cognitive function (6). Chronic neuropathic pain, a frequent secondary complication of SCI, also contributes substantially to the development of both conditions (7). Moreover, pain and reduced physical activity following SCI can impair hippocampal neurons, which play a vital role in cognition and mood regulation (8).

Previous studies mostly focused on the physical or psychological rehabilitation of SCI care. There is a scarcity of randomized controlled trials that particularly address cognitive impairment in this population, let alone studies that jointly address cognitive impairment and depression (9). Action Observation and Motor Imagery (AOMI), a mental simulation process, refers to a person watching a recorded or live demonstration of a movement while simultaneously using imagery to covertly rehearse the same movement without actually executing it (10). AOMI involves the internal simulation of actual movement, thereby inducing neural and autonomic changes similar to those executing real movement (11, 12). As a non-invasive, cost-effective, and accessible therapy, AOMI has been widely applied to physical function improvement, especially for individuals with physical disability or mobility impairment (13). It enables individuals who cannot undergo conventional physical training (e.g., those with severe physical disabilities, troublesome pain conditions, or extensive muscle paralysis) to begin rehabilitation in a safer and less strenuous manner (14).

Recent fMRI studies have demonstrated that AOMI tasks activate brain regions associated with motor execution, emotional processing, and cognitive function, specifically the supplementary motor area, premotor cortex, primary motor cortex, cerebellum, posterior parietal regions, and the basal ganglia (15). Moreover, AOMI could promote neurotrophic factor expression, neuroplasticity, and the recruitment of alternative motor circuits (13). Growing evidence supports the beneficial effects of AOMI interventions on cognitive function and depression among the elderly with mobility impairment (16), post-total hip arthroplasty patients (17), adults with Parkinson’s disease (18), and those with vascular cognitive impairment (19). However, most studies remained at the pilot stage with a moderate to high risk of bias, while optimal intervention dosages have yet to be established. Furthermore, the movement/exercise components of imagery protocols vary across different populations. Based on theoretical foundations and practical evidence, we developed a home-based AOMI intervention specifically tailored for adults with SCI. The primary aim of this study is to assess the feasibility, acceptability, and preliminary effects of this pioneering intervention on cognitive function and depression in SCI. This study will specifically examine the intervention’s effects on attention and executive function, given that these cognitive domains are particularly susceptible to impairment in this population (20).

The second aim of this study is to evaluate the effects of AOMI on pain and self-efficacy for exercise. Preliminary evidence suggests that AOMI may reduce pain perception by sequentially activating motor cortical networks and increasing cortical excitability (21). This may have implications for cognitive impairment and depressive symptoms following SCI, as pain is a risk factor for both. In theory, AOMI could trigger positive changes in the self-efficacy for exercise, thereby facilitating increased physical activity engagement (22). Higher levels of physical activity are associated with a lower incidence of cognitive impairment and depression (23). Furthermore, multimodal MRI will be used to explore the potential neural mechanisms underlying AOMI. These insights can pave the way for updating current clinical practice and offer a deeper understanding of the neuroplasticity and brain’s functional reorganization among the SCI population post-intervention.

The home-based AOMI represents a promising intervention for improving cognitive function and alleviating depression in adults with SCI. However, the current evidence remains limited, underscoring the need for this research to (1) develop and validate population-specific AOMI intervention targeting cognitive function and depression; and (2) elucidate the underlying neurophysiological mechanisms underlying these therapeutic effects in SCI.

## Methods

2

### Study design

2.1

A prospective, assessor-blinded, two-arm pilot randomized controlled trial with repeated measures (pre-, post-intervention, and 1-month follow-up) will be conducted to evaluate the effectiveness of the AOMI intervention among adults with SCI. In total, 46 participants will be randomly assigned to either the intervention group, which will receive an 8-week AOMI intervention combined with basic wheelchair exercises, or the control group, which will watch landscape videos and perform basic wheelchair exercises. Participants will undergo MRI scans at baseline and after the intervention. One-on-one qualitative interviews will be implemented post-intervention to collect participants’ perceptions of effectiveness, intervention acceptability, strengths, limitations, and suggestions for further improvement. Participants’ recruitment began in March 2025. This study protocol complies with the Standard Protocol Items: Recommendations for Interventional Trials Statement (SPIRIT) (24) and the Consolidated Standard of Reporting Trials Statement (CONSORT): extension to randomized pilot and feasibility trials (25) (Figure 1). The protocol was prospectively registered at ClinicalTrials.gov (NCT06708026).

**Figure 1 fig1:**
[figure not shown]
Study flow chart. *ITT, Intention-to-treat.

### Participants

2.2

Participants are being recruited from community centers and non-governmental organizations in Hong Kong using advertisement posters. Eligibility screening for potential participants is conducted via online questionnaires and phone calls. Final enrollment is confirmed during an in-person visit, where participants receive a detailed overview of the study, provide informed consent, and complete a baseline assessment.

Severe cognitive impairment could impair participants’ motor imagery abilities, which may interfere with the assessment of intervention efficacy (26). Therefore, subjects will be included if they are (1) aged 18 years or above; (2) diagnosed with SCI for over 6 months, as per the International Standards for the Neurological Classification of SCI, confirmed by computed tomography or MRI; (3) with stable spinal systems and good vital signs, and residing in the community; (4) having no contraindications for MRI scans (e.g., absence of metal or electronic implants, non-pregnant status, and absence of claustrophobia); (5) having a mobile Internet terminal (usually a smartphone) and proficient independent or caregiver-assisted usage; and (6) able to communicate in Cantonese/Chinese and to provide written informed consent.

The exclusion criteria are as follows: (1) severe impairments in hearing, verbal communication, or vision; (2) participation in concurrent psychotherapy, physiotherapy, exercise, or relaxation interventions; (3) physically active for over 150 min of moderate-intensity exercise per week; (4) diagnosed mental disorders or substance misuse; and (5) severe cognitive impairment [indicated by the Hong Kong Montreal Cognitive Assessment (HK-MoCA) score ≤ 18] (27). No restrictions will be imposed regarding the level, cause, or completeness of the spinal cord injury.

### Randomization and blinding

2.3

Randomization will be performed through the minimization method (28) to balance the pertinent influencing factors for cognitive function and the intervention effectiveness (i.e., motor imagery ability (29), age, and educational level). Minimization entails assigning intervention to succeeding trial participants based on the characteristics of previously enrolled participants (excluding the first participant who receives a random allocation) to enhance balance among the groups in key variables of interest. An independent administrative clerk will conduct this procedure by using the Minim software and will subsequently provide the researcher with a sequentially numbered, sealed, opaque envelope containing the group assignment for the participants. Due to the nature of the intervention, participants and the researchers who will enroll in the intervention process and qualitative interviews will not be blinded. However, the baseline and outcome assessor, as well as the data analyst, will remain blinded to group assignment.

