### Sample size and sampling

2.6

The central limit theorem posits that a minimal sample size of 30–40 is enough for determining the mean, standard deviations, and 95% confidence intervals (58). This pilot RCT aims to assess the feasibility, acceptability, and preliminary effectiveness of the AOMI intervention, utilizing a generally acceptable sample size for preliminary analysis to evaluate intervention feasibility and estimate the between-group effect. Specifically, each study group will have 18 individuals to identify a standardized effect size of 0.40 with 80% power and a two-sided significance level of 5% (59). Taking into account a potential attrition rate of 20%, 23 participants per group (i.e., 46 participants in total) will be recruited by using convenience sampling. For one-on-one interviews, we will use a purposeful sampling of key informants, including those who completed at least 60% of the intervention sessions and those who did not, until we reach information saturation and find no relevant new codes in the data (60).

For MRI scans, a liberal threshold of *α* = 0.05 requires 24 participants (12 per group) to achieve 80% power at the single-voxel level for typical activations (61). To control error rates in multiple comparisons, doubling the number of participants is recommended to maintain this level of power. Due to the challenges of MRI data collection, each group will consist of a minimum of 12 participants undergoing pre- and post-intervention MRI scans. Notably, this sample size aligns with the median sample size observed in highly cited clinical fMRI studies published over the last three decades (62).

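### Section 2.3 names a random element only for the first participant, so the minimisation as written is deterministic apart from ties and later allocations could be predicted well above chance

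*Protocol article*

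**What the plan says.** Section 2.3 (Randomization and blinding) uses minimisation on three factors: "motor imagery ability (29), age, and educational level". It explains the method in one sentence: "Minimization entails assigning intervention to succeeding trial participants based on the characteristics of previously enrolled participants (excluding the first participant who receives a random allocation". It gives no assignment probability, tie rule, factor weights or cut-points.

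On concealment it says "An independent administrative clerk will conduct this procedure by using the Minim software"; the clerk then passes the researcher a numbered, sealed, opaque envelope. On blinding, "participants and the researchers who will enroll in the intervention process and qualitative interviews will not be blinded", while the baseline and outcome assessor and the data analyst are blinded.

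Other relevant sections:
- Section 2.2: recruitment by posters, screening by online questionnaire and phone, and enrolment confirmed at an in-person visit.
- Table 1 (Section 2.5): screening and consent come before T0; motor imagery ability is first measured at T0.
- Section 2.6: the 46 participants "will be recruited by using convenience sampling".
- Section 2.1: recruitment began in March 2025.

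**The concern.** The text does more than leave out an assignment probability. It says where chance enters (the first participant) and contrasts that with the rule for everyone else. Read plainly, allocations from the second onward are fixed by the factor levels and arms of earlier participants, except when the two arms tie.

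A sealed envelope protects against someone reading the next assignment, but not against someone working it out. The intervention researchers are unblinded and so know past arms. In a trial of 46 assessed on one campus, a small team could keep count. If anyone with a say in whether or when a person is enrolled could anticipate the arm, selection bias could enter, and blinded outcome assessment would not remove it. A nearly deterministic sequence also weakens the randomisation basis for the p-values. The pilot is meant to inform a full-scale trial, which could inherit the same allocation scheme.

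**Working it through.** The documents state no predictability figure, so there is none to reproduce. The check asks how predictable the rule would be if applied as written.

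**Inputs from the protocol article.** N = 46, two arms of 23 (Section 2.6); three minimisation factors and a random first allocation (Section 2.3).

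**Assumptions not in the documents.** Each factor has 2 to 3 equally likely levels; factors have equal weight; ties are broken at random.

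**Rule simulated.** For a new participant with levels x1, x2, x3, compute S = Σk [nA(k, xk) − nB(k, xk)], where n counts earlier participants in that arm who share the level. If S < 0 assign A; if S > 0 assign B; if S = 0 toss a fair coin. With a random element, the arm indicated by S is assigned with probability p instead of 1.

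**Share determined, p = 1.** Mean ties per trial, including the first participant, are about 9.97 with levels (2,2,2) and 10.42 with (3,3,3).
- (46 − 9.97)/46 = 0.783
- (46 − 10.42)/46 = 0.773

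**Fully informed guesser, p = 1.** Right on every determined allocation and on half the ties:
- 0.783 + 0.217/2 = 0.892
- 0.773 + 0.227/2 = 0.887

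The simulated rates are 0.891 and 0.887.

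**Fully informed guesser, p = 0.8.** Mean ties are 7.40 and 8.00, so the non-tied share is 0.839 and 0.826:
- 0.8 × 0.839 + 0.5 × 0.161 = 0.752
- 0.8 × 0.826 + 0.5 × 0.174 = 0.748

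The simulated rates are 0.751 and 0.748.

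**Correct guesses by what the guesser knows** (chance is 50%):

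| Knowledge | p = 1 | p = 0.8 |
|---|---|---|
| All three factors, cut-points, past arms | about 89% | about 75% |
| Two of three factors, past arms | about 80–84% | about 69–71% |
| Arm totals only | about 68–72% | about 62–64% |

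The range in the second row depends on the level sets and on whether arm totals are used when the two known factors tie.

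**Sensitivity at p = 1.** Allowing up to 4 levels per factor, or measuring imbalance as the sum of absolute differences, widens the results to 73–78% determined, 86–89% correct with full knowledge, and 65–72% with arm totals only.

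**Cost in balance.** Moving from p = 1 to p = 0.8 raises the mean absolute difference in arm totals from about 0.2–0.6 to about 1 participant.

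**The case against.** The strongest objection is that determinism is inferred. The sentence is a one-line definition in a condensed article, the word deterministic does not appear, and the software or full protocol may set a random element. Part of this stands: the actual setting is unknown and must be checked first. It does not dispose of the point, because the article assigns randomness to the first participant only. If more is used, the sentence is wrong and needs correcting.

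A reader might also infer that unblinded staff could predict about 90% of allocations. The documents do not support that. The figure is a ceiling that needs all three factor levels, the cut-points and every past arm. An independent clerk runs the procedure, and a blinded assessor collects the imagery score at T0, after screening and consent. No section says that unblinded staff screen or enrol participants or hold the running table. Convenience sampling by poster does not in itself show that staff control the order of entry. This part of the objection stands in full.

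Three further points are fair. A probability of 0.8 still leaves a fully informed guesser right about 75% of the time, so restricting access to the running table matters as much as the probability. Recruitment has begun, so any change falls mid-trial. And this is a pilot that claims only preliminary effectiveness, which limits the harm.

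**Conclusion.** The point holds as a conditional risk. As written, the minimisation is deterministic apart from ties, and the stated concealment steps do not prevent prediction from past assignments. Under the assumed levels, equal weights and random tie-breaking, about 77% to 78% of the 46 allocations would be determined. Correct guessing would range from about 68–72% (arm totals only) to about 89% (full knowledge), against 50% by chance. Even the least informed guesser therefore does clearly better than chance.

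What is not established is that anyone who recruits has the information needed, or that the software is in fact set to a deterministic rule. The text fails to exclude the risk; it does not show a breach. It is worth correcting because the remedy is cheap.

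**What to change.** 1. Have the clerk check and report the assignment probability and tie rule set in the software.
2. If the rule is deterministic, assign the imbalance-reducing arm with a fixed probability below 1 (e.g. 0.8) for all remaining participants, record the date of the change, and state it in Section 2.3. If a random element is already in use, correct the sentence in Section 2.3.
3. In either case, keep the running table of factor levels and arms from anyone who screens or enrols, and say so.
4. Pre-specify adjustment for motor imagery ability, age and educational level in the GEE. Section 2.7.1 now adjusts only for differences found in the baseline comparison; these three covariates are named only in the MRI analyses (Section 2.7.3).

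The cost is a software setting, a short dated amendment made while recruitment is under way, one added line in the analysis plan, and slightly looser balance (about 1 participant's mean difference in arm totals instead of about 0.2–0.6).

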### Interventions

2.4

All participants will perform the same basic wheelchair exercises at home, following an instructional video. The video, which contains a set of low-intensity warm-up exercises, was developed by two experienced physiotherapists in Hong Kong (30). All participants will receive weekly phone calls to monitor progress and provide support during the training period. In order to avoid potential adverse events associated with the exercise (i.e., falls, joint pain, muscle strain, stress fracture, and exacerbation of existing injuries and disease symptomology) (31), the intensity of the workouts will be evaluated using the Borg ratings of perceived exertion (RPE), which should be maintained at less than 13 scores to ensure light to moderate intensity (32).

#### Intervention group

2.4.1

Participants allocated to the AOMI group will receive, following the 10-min basic wheelchair exercise, a session of 20-min AOMI training. Based on the evidence from our scoping review, the intervention dosages are set as 3 sessions a week for a total of 8 weeks (Supplementary Table S1) (33). AOMI session duration of 20 min is widely adopted to minimize mental fatigue while maintaining the beneficial effects (34, 35). The AOMI training will be delivered through video recordings with verbal instructions that can be accessed via smartphones for streaming. After the randomization and prior to the intervention, participants will be informed in lay language about the concept of AOMI and its application in neurorehabilitation. Subsequently, they will engage in a face-to-face AOMI practice seminar guided by a trained researcher with motor imagery qualification. After the familiarization and demonstration, participants will receive the videos for AOMI. They will be required to watch the videos while simultaneously engaging in motor imagery of the same action at home.

The typical model, which is denoted by the acronym of AOMI components (i.e., PETTLEP, Physical, Environment, Task, Timing, Learning, Emotion, Perspective), was adopted for AOMI strategy development (36). These seven words represent a minimum checklist of AOMI components required to closely simulate real movements, aiming for optimal functional and physical equivalence. Based on the model and evidence from the scoping review (33), the home-based AOMI strategy specifically includes the following: asking participants to conduct AOMI while holding sport-specific implements, wearing comfortable clothing, and adopting the sitting position (Physical), and, where possible, practicing in a quiet home setting (Environment). The imagery is guided in synchrony with the real-time video with verbal instructions (Timing). To enhance familiarity with MI tasks, strategies such as gradual learning and repetition are employed (Learning). Motivational instructions combined with arousal-enhancing music are employed to facilitate the recall and recreation of exercise-associated affective states (Emotion). Furthermore, participants will be instructed and specified informed on the imagery viewpoint (Perspective). To maintain attention and enhance compliance (37), we designed three sets of wheelchair exercises and one set of walking activities as imagery contents (Task). These were presented in video format, based on the Canadian Spinal Cord Injury Physical Activity Guidelines (38) and our previous physical–psychological interventions specifically tailored for Hong Kong SCI populations (30). The imagery contents will change biweekly and become consistent every 2 weeks. Further details of the AOMI strategy and the specific tasks for motor imagery are provided in Supplementary Tables S2, S3, respectively.

